#### **7.6.1 Unblinding of all trial participants (protocol V19.0)**

All trial participants will be unblinded following the approval of protocol V19.0. This follows the earlier completion of the primary efficacy analysis, the significant level of unblinding that has occurred due to the national vaccine rollout already within the trial and the fall in transmission of SARS-CoV-2 within the UK. Following unblinding and provision of COVID-19 vaccination (in or outside the study), participants will continue to follow all other study procedures and should continue to complete the visit schedule for their group. This will enable further analysis of immunogenicity, safety and immunological correlate of protection analysis.

Provision of treatment for controls is described in section 8.11

#### **7.6.2 Unblinded participants who are eligible to receive an approved or licensed SARS-CoV-2 vaccine**

For those who choose to receive a deployed vaccine:

An extra visit A may be arranged (where possible and practical to do so) for those who are offered and are willing to accept a SARS-CoV-2 approved or licensed vaccine where a blood sample for immunogenicity assessment (up to 50mL) may be drawn, regardless of which arm of the study they

have been allocated to (ChAdOx1 nCoV-19 or MenACWY) or their COVID-19 status. SAEs and AESIs will be collected at this point. Participants will then follow their normal schedule of attendances according to the group they were previously randomised or allocated to.

For those who have received a single dose of the ChAdOx1 nCov-19 vaccine:

Those who are eligible to receive an approved or licensed SARS-CoV-2 vaccine, and who after unblinding are found to have received only a single dose of ChAdOx1 nCoV-19 will be given an option to receive a booster standard dose (ChAdOx1 nCoV-19  $3.5\text{--}6.5 \times 10^{10}$  vp) at an extra visit B, instead of a deployed vaccine, as per national policy. The safety and benefit of mixed vaccine schedules is unknown. The extra visit B will take place  $\geq 4$  weeks post prime and should be conducted at the earliest possibility. The participant will be counselled on the timings of the planned vaccination and will be able to decide which vaccine to choose. SAEs and AESIs will be collected at this point. A blood sample for immunogenicity assessment (up to 50mL) may be drawn and participants will then follow their normal schedule of attendances according to the group they were previously randomised or allocated to. When participants have been unblinded they and the GP will receive a letter detailing the vaccines received in the study.

## **8 INVESTIGATIONAL PRODUCT**

### **8.1 Description of ChAdOx1 nCoV-19**

ChAdOx1 nCoV-19 vaccine consists of the replication-deficient simian adenovirus vector ChAdOx1, containing the structural surface glycoprotein (Spike protein) antigens of SARS-CoV-2.

### **8.2 Supply**

ChAdOx1 nCoV-19 has been formulated and vialled at Advent S.r.l. (Pomezia, Italy). Labelling has been done at the Clinical BioManufacturing Facility (University of Oxford) or Advent S.r.l. (Pomezia, Italy). It will be certified by a Qualified Person (QP) at the Clinical BioManufacturing Facility (University of Oxford) before release and transfer to the clinical site.

ChAdOx1 nCoV-19 (AZD1222) has been formulated at Cobra Biologics Ltd, vialled at Symbiosis Pharmaceutical Services, and labelled and packaged at Thermo Fisher Scientific (Hertfordshire, United Kingdom). It will be certified by a Qualified Person (QP) at the MedImmune Pharma, BV

(Nijmegen, The Netherlands) or MedImmune Ltd (Cambridge, United Kingdom) before release and transfer to the clinical site.

ChAdOx1 nCoV-19 (Covishield) has been formulated and vialled at Serum Institute of India Pvt. Ltd. Labelling and QP certification was done at Bilthoven Biologicals (Bilthoven, Netherlands) before release and transfer to the clinical site.

### **8.3 Storage**

The vaccine manufactured by Advent is stored at nominal -80°C (+/- 20 °C) in a secure freezer, at the clinical site. The vaccines manufactured by Cobra Biologics Ltd and Serum Institute of India are stored at 2-8°C in a secure fridge, at the clinical site. All movements of the study vaccines will be documented in accordance with existing standard operating procedure (SOP). Vaccine accountability, storage, shipment and handling will be in accordance with relevant SOPs and forms. To allow for large number of participants to receive the vaccine in a short time period, additional clinic locations may be used. In this instance vaccines will be transported in accordance with local SOP's and approvals as required

### **8.4 Administration**

On vaccination day, ChAdOx1 nCoV-19 will be allowed to thaw to room temperature and will be administered in accordance with trial specific instructions or stored at 2-8 for a maximum of up to 48 hours, where multiple doses are required from a single vial. The vaccine manufactured by Cobra Biologics is a multi-dose vial which is stored at 2-8 degrees and does not require thawing. If the vaccine is stored outside of 2-8 it must be used within 6 hours. If stored at 2-8°C after the first vial puncture, it can be used within 48 hours. The Covishield vaccine is stored at 2-8°C at all times unless it is being used for the dose preparation process. Total time from needle puncture of the vaccine vial to the start of administration must not exceed 6 hours at 2-8°C. If preparation time exceeds the time limit, a new dose must be prepared. The vaccine will be administered intramuscularly into the deltoid of the non-dominant arm (preferably). ). Prior to protocol V19.0: All volunteers will be observed in the unit for a minimum of 15 minutes (+15 minutes) after vaccination. Following protocol V19.0 approval: In line with UK Greenbook recommendations, participants do not need to be routinely observed following either prime (1st) or boost (2nd) dose of ChAdOx1 nCoV-19. During administration of the investigational products, Advanced Life Support drugs and resuscitation equipment will be

immediately available for the management of anaphylaxis. Vaccination will be performed and the IMPs handled according to the relevant SOPs.

## 8.5 Rationale for selected dose

The dose to be administered in this trial have been selected on the basis of clinical experience with the ChAdOx1 adenovirus vector expressing different inserts and other similar adenovirus vectored vaccines (eg. ChAd63).

A first-in-man dose escalation study using the ChAdOx1 vector encoding an influenza antigen (FLU004), safely administered ChAdOx1 NP+M1 at doses ranging from  $5 \times 10^8$  to  $5 \times 10^{10}$  vp. Subsequent review of the data identified an optimal dose of  $2.5 \times 10^{10}$  vp balancing immunogenicity and reactogenicity. This dose has subsequently been given to over hundreds of volunteers in numerous larger phase 1 studies at the Jenner Institute. ChAdOx1 vectored vaccines have thus far demonstrated to be very well tolerated. The vast majority of AEs have been mild-moderate and there have been no SARs until this date.

Another simian adenovirus vector (ChAd63) has been safely administered at doses up to  $2 \times 10^{11}$  vp with an optimal dose of  $5 \times 10^{10}$  vp, balancing immunogenicity and reactogenicity.

MERS001 was the first clinical trial of a ChAdOx1 vectored expressing the full-length Spike protein from a separate, but related betacoronavirus. ChAdOx1 MERS has been given to 31 participants to date at doses ranging from  $5 \times 10^9$  vp to  $5 \times 10^{10}$  vp. Despite higher reactogenicity observed at the  $5 \times 10^{10}$  vp, this dose was safe, with self-limiting AEs and no SARs recorded. The  $5 \times 10^{10}$  vp was the most immunogenic, in terms of inducing neutralising antibodies against MERS-CoV using a live virus assay. Given the immunology findings and safety profile observed with a ChAdOx1 vectored vaccine against MERS-CoV, the  $5 \times 10^{10}$  vp dose was chosen for ChAdOx1 nCoV-19.

The Clinical BioManufacturing Facility (CBF), who manufactured and tested batches 02P20-01 and 02P20-02 for the COV001 trial, determined vp/mL for Advent manufactured batch(es). This was done using a spectrophotometry-based methodology documented in their internal SOP (SOP A104). The doses to be administered in COV002, on Advent manufactured batches, will be determined by both methods (Abs260 and qPCR). Overseas studies conducted on Advent batch(es) will be dosed based on Advent's qPCR method. The University of Oxford is also performing a number of for information only tests for ChAdOx1 nCoV-19 batch(es) manufactured by Advent to demonstrate comparability

between the different manufacturing processes and suitability of a reconstitution process involving dilution of the product with 0.9 % (w/v) saline that will be managed using local clinical trial SOPs available at each site/location.

For Advent Lot Number K.0007 the concentration is  $1.7 \times 10^{11}$  vp/mL (qPCR) which has been assessed by the CBF as equivalent to  $3.89 \times 10^{11}$  vp (Abs 260).

An analytical comparability assessment of ChAdOx1 nCoV-19 (AZD1222) manufactured by CBF, Advent and Cobra Biologics was conducted using a comprehensive set of physiochemical and biological release and characterization tests. In order to support the analytical comparability assessment, A260 testing of Advent's process (K.0007, K.0008, and K.0009 lots) was performed, where corrections to the absorbance due to excess polysorbate 80 were made to compensate for polysorbate 80 concentrations above the formulation target of 0.1% (w/v).

Differences in strength related attributes (ie, virus particle concentration, virus genome concentration, and infectious virus concentration) are noted. These differences in strength is further examined for potential impact on clinical dosing. The target clinical dosage of CBF's product is  $5 \times 10^{10}$  viral particles per dose based on vp/mL concentration determined by UV spectroscopy (A260), whereas that of Advent's product is  $5 \times 10^{10}$  viral genome copies per dose based on vg/mL concentration determined by qPCR. The target clinical dosage of Symbiosis' product is  $3.5 - 6.5 \times 10^{10}$  viral particles per dose based on the vp/mL concentration determined by A260, with a 0.5 mL dosing volume. This dosing range is based on a target  $5 \times 10^{10}$  viral particles per dose and a  $\pm 30\%$  range to take into account process and method variabilities. The planned clinical dosage of Symbiosis' product is compared to that of CBF and Advent products, the resulting Symbiosis' product dosage at 0.5 mL for lot 20481A is somewhat lower in total viral particle per dose (20% from the lower range limit), slightly higher in total viral genome copies per dose (12% from the higher range limit), and slightly lower in total infectious particle per dose (8% from the lower range limit). These differences are considered to be comparable to or within the variabilities from the analytical methods used in concentration determination (A260, qPCR, and infectivity) and the dosing volumes during clinical administration. In summary, with a 0.5 mL dosing volume for Symbiosis' product, strength difference from CBF and Advent products is not expected to have significant clinical impact in terms of reactogenicity and immunogenicity/efficacy.

Manufacturing of ChAdOx1 nCoV-19 is also taking place at Serum Institute of India (SII). The vaccine is manufactured under the named ChAdOx1 nCoV-19 (Covishield). The target clinical dose for ChAdOx1 nCoV-19 (Covishield) is nominal  $5 \times 10^{10}$  viral particles per dose based on vp/mL concentration determined by UV spectroscopy. An analytical comparability assessment of ChAdOx1 nCoV-19 manufactured by Advent, Cobra Biologics and SII was conducted using a comprehensive set of physiochemical and biological release and characterization tests. The details are available in the IMPD. The planned clinical dosage of SII's product is compared to that of Cobra and Advent products, with a dosing volume of 0.5 mL.

CONFIDENTIAL

Table 14 Clinical Strengths of ChAdOx1 nCoV-19 (AZD1222) Drug Product

| Strength Attribute                                      | CBF                   |                       | Advent                |                       |                       | Cobra                |
|---------------------------------------------------------|-----------------------|-----------------------|-----------------------|-----------------------|-----------------------|----------------------|
|                                                         | Lot 02P20-01          | Lot 02P20-02          | Lot K.0007            | Lot K.0008            | Lot K.0009            | Lot 20481A           |
| Concentration                                    |                       |                       |                       |                       |                       |                      |
| Virus particle concentration ( $A_{260}$ ) (vp/mL)      | $1.49 \times 10^{11}$ | $1.22 \times 10^{11}$ | $3.12 \times 10^{11}$ | $3.16 \times 10^{11}$ | $2.45 \times 10^{11}$ | $0.8 \times 10^{11}$ |
| Virus genome concentration (qPCR) (vg/mL)               | $1.7 \times 10^{11}$  | Not tested            | $1.7 \times 10^{11}$  | $2.1 \times 10^{11}$  | $1.4 \times 10^{11}$  | $1.3 \times 10^{11}$ |
| Infectious particle concentration (ifu/mL) a | $2.6 \times 10^9$     | Not tested            | $2.9 \times 10^9$     | $3.0 \times 10^9$     | $2.4 \times 10^9$     | $1.3 \times 10^9$    |
| Target Clinical Dosage                           |                       |                       |                       |                       |                       |                      |
| Equivalent DP volume per dose (mL)                      | 0.34                  | 0.41                  | 0.294                 | 0.235                 | 0.356                 | 0.50                 |
| Dosing of virus particle (vp/dose)                      | $5.1 \times 10^{10}$  | $5.0 \times 10^{10}$  | $9.2 \times 10^{10}$  | $7.4 \times 10^{10}$  | $8.7 \times 10^{10}$  | $4.0 \times 10^{10}$ |
| Dosing of viral genome (vg/dose)                        | $5.8 \times 10^{10}$  | NA                    | $5.0 \times 10^{10}$  | $4.9 \times 10^{10}$  | $5.0 \times 10^{10}$  | $6.5 \times 10^{10}$ |
| Dosing of infectious particle (ifu/dose)                | $8.8 \times 10^8$     | NA                    | $8.5 \times 10^8$     | $7.1 \times 10^8$     | $8.5 \times 10^8$     | $6.5 \times 10^8$    |

a ifu = infectious units; NA = not applicable; vp = virus particle; vg = virus genome

a **Testing performed using the Advent infectivity assay.**

## 8.6 Minimising environmental contamination with genetically modified organisms (GMO)

The study will be performed in accordance with the current version of the UK Genetically Modified Organisms (Contained Use) Regulations. Approved SOPs will be followed to minimise dissemination of the recombinant vectored vaccine virus into the environment. GMO waste will be inactivated according to approved SOPs.

## 8.7 Control vaccine

Participants who are allocated to the control groups will receive one or two injections of MenACWY vaccine instead of ChAdOx1 nCoV-19. Either of the two licensed quadrivalent protein-polysaccharide conjugate vaccine MenACWY vaccines will be used, i.e.:

- Nimenrix (Pfizer). The licensed posology of this vaccine for those over 6 months of age is a single (0.5ml) intramuscular dose, containing 5mcg each of *Neisseria meningitidis* group A, C, W and Y polysaccharide, each conjugated to 44 mcg tetanus toxoid carrier protein.
- Menveo (Glaxosmithkline). The licensed posology of this vaccine for those 2 years of age and over is a single (0.5ml) intramuscular dose, containing
  - 10 mcg meningococcal group A polysaccharide, conjugated to 16.7 to 33.3 mcg *Corynebacterium diphtheriae* CRM197 protein
  - 5mcg meningococcal group C polysaccharide, conjugated to 7.1 to 12.5 mcg *C. diphtheriae* CRM197 protein
  - 5mcg meningococcal group W polysaccharide, conjugated to 3.3 to 8.3 mcg *C. diphtheriae* CRM197 protein
  - 5mcg meningococcal group Y polysaccharide, conjugated to 5.6 to 10.0 mcg *C. diphtheriae* CRM197 protein

The summary of product characteristics for both vaccines allows for administration of a booster dose if indicated by ongoing risk, therefore allows for the two doses administered to a subset of participants in this study. Similarly, previous receipt of either vaccine (or a plain polysaccharide quadrivalent meningococcal A, C, W and Y vaccine) will not be a contraindication to receiving a further vaccine in this study.

Participants will be blinded as to which injection they are receiving. A vaccine accountability log of MenACWY will be maintained at each trial site. There will be no additional labelling of these vaccines beyond their licensed packaging.

MenACWY will be stored in a locked (or access controlled) refrigerator (2°C – 8°C) at the sites, as per SmPC.

## **8.8 Compliance with Trial Treatment**

All vaccinations will be administered by the research team and recorded in the CRF. The study medication will be at no time in the possession of the participant and compliance will not, therefore, be an issue.

## **8.9 Accountability of the Trial Treatment**

Accountability of the IMP and MenACWY will be conducted in accordance with the relevant SOPs.

## **8.10 Concomitant Medication**

As set out by the exclusion criteria, volunteers may not enter the study if they have received: any vaccine in the 30 days prior to enrolment, any investigational product within 30 days prior to enrolment or if receipt is planned during the study period, or if there is any chronic use (>14 days) of any immunosuppressant medication within 6 months prior to enrolment or if receipt is planned at any time during the study period (topical steroids are permitted).

Participants on continuous use of oral anticoagulants, such as coumarins and related anticoagulants (i.e. warfarin) or novel oral anticoagulants (i.e. apixaban, rivaroxaban, dabigatran and edoxaban) will be excluded from this trial, as per the exclusion criteria.

Participants in groups 4 and 6 will be advised to take Paracetamol after vaccination at 1g every 4-6 hours for the first 24 hours (maximum dose 4g within 24 hours). This will not be a requirement for study participation, and participants will have the option to not follow the advice.

Participants who become eligible for a SARS-CoV-2 vaccine according to government guidance will be able to receive the vaccine as recommended. We will advise participants to allow a minimum period of 2 weeks between vaccination with MenACWY and the SARS-CoV-2 vaccine for those in the control

group and 3 weeks between vaccination with ChAdOx1 nCoV-19 and the deployed SARS-CoV-2 vaccine. Participants will be asked to record the date and type of vaccine received.

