The use of prophylactic paracetamol reduces the incidence and severity of fever and other adverse events following immunisation (AEFI). It has been previously recommended following Meningococcal B vaccine administration without negatively impacting its immunogenicity profile (reference: Bexsero

SmPC). Given the potential higher reactogenicity profile of ChAdOx1 nCoV-19 at  $5 \times 10^{10}$ vp doses, a prophylactic paracetamol dose has been introduced in order to minimise severity of commonly observed local and systemic AEFI.

A batch comparison group (Group 5) has been included to assess potential differences in safety, reactogenicity and immunogenicity profiles across different ChAdOx1 nCoV-19 vaccine manufacturers.

Group 6 has been added to provide a comparison between efficacy at  $5 \times 10^{10}$ vp dose on Abs260 and  $5 \times 10^{10}$  vp qPCR methods from different vaccine manufacturers.

Groups 7 and 8 have been added to provide safety, reactogenicity and immunogenicity data in older age groups receiving a  $5 \times 10^{10}$ vp dose on qPCR, and replicate the study design in groups 1 and 2.

Group 4b has been added to provide immunogenicity data on homologous prime-boost at  $5 \times 10^{10}$ vp (Abs260) prime and  $2.2 \times 10^{10}$ vp (qPCR) boost, where up to 100 volunteers aged 18-55 initially recruited into group 4a will receive a booster dose of the vaccine 4-6 weeks apart.

Groups 4c and 6b have been added following interim immunogenicity results on homologous prime-boost groups showing improved neutralising antibody titres after 2 doses when compared to 1 dose regimen.

Groups 9 and 10 have been added as part of main safety and efficacy assessments in older age groups (56 – 69 years and 70 years and over) and removed from groups 4 and 6, as no vaccinations have been given to these age groups at the time of these group additions.

Group 11 has been added as an open-label and not randomised group to investigate the impact of previous ChAdOx1 vectored vaccines in immune responses elicited by ChAdOx1 nCoV-19.

Group 12 has been added as an open-label and not randomised group to investigate the safety and immunogenicity of ChAdOx1 nCoV-19 in people living with HIV.

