After review of all available data from animal studies and at least 4 weeks safety and immunogenicity data from the first 54 participants receiving ChAdOx1 nCoV-19 in COV001, following DSMB review, enrolment into Groups 1, 4, 5 & 6 will commence. A minimum of 7 days safety data from group 1 will be reviewed by the DSMB prior to enrolment of participants into group 2. Participants will be randomised to ChAdOx1 nCoV-19/MenACWY on a 3:1:3:1 ratio in groups 1 and 7, and 5:1:5:1 ratio in groups 2 and 8, 1:1 in groups 4, 5a, 5b, 5c, 6, 9 and 10, and 5:1 in group 5d. Groups 5e and 5f will be open label and therefore, volunteers will not be randomised. Participants in groups 4, 6, 9 and 10 will be advised to take prophylactic paracetamol for 24 hours (1000 mg every 4-6 hours) from the time of vaccination to reduce the likelihood of fever. The sequence of enrolment of participants over the age of 56 years is outlined in section 7.3.2.2. Up to 100 volunteers in group 4 will be invited to receive a booster dose of  $2.2 \times 10^{10}$  vp (qPCR) 4-6 weeks after prime. All remaining volunteers in group 4 and all participants in group 6 will be invited to receive a booster dose of 0.5mL ( $3.5 - 6.5 \times 10^{10}$  vp, Abs 260, corrected for PS80) at least 4 weeks after prime. Participants who were originally randomised to receive a single dose in groups 1 (a1 and a2), 2 (a1 and a2) and 5 (a1 and a2) will be invited to receive a booster dose of 0.5mL ( $3.5 - 6.5 \times 10^{10}$  vp, Abs 260, corrected for PS80) at the earliest available opportunity, with a minimum 4 weeks interval from prime.

Safety will be assessed in real time. The DSMB will periodically assess safety and efficacy data every 4-8 weeks and/or as required.

Participants will be followed over the duration of the study to record adverse events and episodes of virologically confirmed symptomatic COVID-19 cases. Participants will be tested for COVID-19 if they present with a new onset of fever ( $\geq 37.8$  C) OR cough OR shortness of breath OR anosmia/ageusia.

Weekly testing for PCR+ infection with SARS-CoV-2 using home test kits will also be undertaken in partnership with the Department of Health and Social care national community testing programme, subject to testing resource availability.

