#### **6.3.1 Inclusion Criteria**

The volunteer must satisfy all the following criteria to be eligible for the study:

- Adults aged 18 - 55 years (groups 4, 5, 6 and 11)
- Adults aged 56-69 years (groups 1, 7, and 9)

- Adults aged 70 years and older (groups 2, 8, and 10)
- Able and willing (in the Investigator's opinion) to comply with all study requirements.
- Willing to allow the investigators to discuss the volunteer's medical history with their General Practitioner and access all medical records when relevant to study procedures.
- For females of childbearing potential only, willingness to practice continuous effective contraception (see below) during the study and a negative pregnancy test on the day(s) of screening and vaccination.
- Agreement to refrain from blood donation during the course of the study.
- Provide written informed consent.

Additional Inclusion criteria to Group 12 (HIV sub-study):

- HIV positive
- Receiving antiretroviral therapy
- Undetectable HIV viral load
- CD4>350 cells/mL

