### *7.3.2.1 Vaccination*

All vaccines will be administered intramuscularly according to specific SOPs. The injection site will be covered with a sterile dressing and the volunteer will stay in the trial site for observation for a minimum of 15 minutes (+15 minutes), in case of immediate adverse events. The sterile dressing will be removed and injection site inspected.

In groups 1-3, 5, 7, 8, 11 and 12 and in a subset of volunteers in groups 4, 6, 9 and 10 (n=up to 1000, in each groups 4 and 6 and approximately 500 in each of groups 9 and 10), participants will be given an oral thermometer, tape measure and diary card (paper or electronic), with instructions on use. The approximate 3000 participants in groups 4, 6, 9 and 10 that are required to complete diaries will be allocated according to site. The allocation will ensure distribution of ages. All participants will be given the emergency 24 hour telephone number to contact the on-call study physician if needed. Volunteers will be instructed on how to self-assess the severity of these AEs. There will also be space on the diary card to self-document unsolicited AEs, and whether medication was taken to relieve the symptoms. Participants in groups 4, 6, 9 and 10 will be advised to take prophylactic paracetamol for 24 hours after vaccination and will record this in the e-diary (up to 1,000 participants in each of groups 4 and 6, and approximately 500 in each of groups 9 and 10 only). Participants in groups 1-3 and 5, 7, 8 and 11 will be asked to report on solicited AEs for 7 days and unsolicited AEs for 28 days. The subset of approximately 3000 participants in groups 4, 6, 9, and 10 will be asked to report solicited and unsolicited AEs for 7 days only. Participants in group 12 will be asked to report on solicited local and systemic AEs for 7 days and unsolicited AEs for 28 days.

Diary cards will collect information on the timing and severity of the following solicited AEs:

Table 3. Solicited AEs as collected on post vaccination diary cards

| Local solicited AEs | Systemic solicited AEs |
|---------------------|------------------------|
| Pain                | Fever                  |
| Tenderness          | Feverishness           |
| Redness             | Chills                 |
| Warmth              | Joint pains            |
| Itch                | Muscle pains           |
| Swelling            | Fatigue                |
| Induration          | Headache               |

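### Section 8.10 states the 4 g in 24 hours paracetamol maximum for groups 4 and 6 only, although Section 5 gives groups 9 and 10 the same regimen

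*Protocol*

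**What the plan says.** Four places in the protocol deal with prophylactic paracetamol.

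- **Section 5 (Trial Design):** "Participants in groups 4, 6, 9 and 10 will be advised to take prophylactic paracetamol for 24 hours (1000 mg every 4-6 hours"). No maximum is given for any group.
- **Section 6.3.2 (Exclusion Criteria):** the additional criterion on reactions to paracetamol covers groups 4, 6, 9 and 10. It carries a note of caution about chronic users and gives no dose limit.
- **Section 7.3.2.1 (Vaccination):** "Participants in groups 4, 6, 9 and 10 will be advised to take prophylactic paracetamol for 24 hours after vaccination". It gives neither a dose nor a maximum.
- **Section 8.10 (Concomitant Medication):** "Participants in groups 4 and 6 will be advised to take Paracetamol after vaccination at 1g every 4-6 hours" for the first 24 hours, with the limit "maximum dose 4g within 24 hours". It also says that following the advice is optional.

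On who is affected, Section 3.4 explains that "Groups 9 and 10 have been added as part of main safety and efficacy assessments in older age groups". Section 6.3.1 sets the ages: "Adults aged 56-69 years (groups 1, 7, and 9") and "Adults aged 70 years and older (groups 2, 8, and 10").

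**The concern.** Three sections apply paracetamol to four groups. The fourth section, which is the only one with a daily limit, applies it to two. For groups 4 and 6 the reader can combine Sections 5 and 8.10 and arrive at a complete instruction. For groups 9 and 10 the dose and interval can be found, but not the maximum.

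The groups without a written limit are the older ones. Groups 4 and 6, which have one, are aged 18-55. The protocol does contain some protection for everyone: it excludes severe or uncontrolled liver disease and current alcohol dependency, urges caution with chronic paracetamol users, and in Section 7.3.2.1 provides that "All participants will be given the emergency 24 hour telephone number". None of these states how much may be taken in a day.

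The point is one of participant safety and clear instruction. It does not touch the sample size, the type 1 error, the efficacy analysis or the reactogenicity comparisons.

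**Working it through.** **Inputs**

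- Dose: 1 g (Sections 5 and 8.10).
- Interval *t*: 4 to 6 hours (Sections 5 and 8.10).
- Duration: 24 hours (Sections 5, 7.3.2.1 and 8.10).
- Maximum: 4 g in 24 hours (Section 8.10, groups 4 and 6).
- Planned size of groups 9 and 10: 1,000 each, plus or minus 10% (Section 5).

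**Step 1. Does the maximum add anything to the interval?** With doses at hours 0, *t*, 2*t* and so on, counting those before hour 24, the number of doses is ceil(24/*t*) and the total is that number times 1 g. The fifth dose, which takes the total past 4 g, falls at hour 4*t*.

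| Interval *t* | Doses = ceil(24/*t*) | Total | Total / 4 g | Hour of fifth dose |
|---|---|---|---|---|
| 4 h | ceil(6) = 6 | 6 g | 1.50 | 16 |
| 4.5 h | ceil(5.33) = 6 | 6 g | 1.50 | 18 |
| 4.8 h | ceil(5) = 5 | 5 g | 1.25 | 19.2 |
| 5 h | ceil(4.8) = 5 | 5 g | 1.25 | 20 |
| 5.9 h | ceil(4.07) = 5 | 5 g | 1.25 | 23.6 |
| 6 h | ceil(4) = 4 | 4 g | 1.00 | none before 24 |

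The plan's own 4 g is therefore the total of the 6-hourly schedule. Any regular interval from 4 h to under 4.8 h gives 6 g, and from 4.8 h to under 6 h gives 5 g. The maximum restricts almost the whole permitted range of intervals.

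**Step 2. Who has the maximum in writing?**

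| Instruction | Groups 4 and 6 | Groups 9 and 10 |
|---|---|---|
| Advised to take paracetamol | Sections 5, 7.3.2.1, 8.10 | Sections 5, 7.3.2.1 |
| 1 g every 4-6 h for 24 h | Sections 5, 8.10 | Section 5 |
| Maximum 4 g in 24 h | Section 8.10 | nowhere |

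**Step 3. How many people does the uncapped wording cover?** 1,000 × 0.9 = 900 to 1,000 × 1.1 = 1,100 planned participants in each of groups 9 and 10. This is the reach of the wording. It is not an estimate of how many would exceed 4 g, and the protocol gives no basis for such a rate.

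**Step 4. Is the wording still live in this version?** Most scheduled doses in these groups may already have been given, which is an inference from how late this version is. Table 11 keeps an optional vaccination at Extra Visit B for participants in groups 9 and 10 who have not had their second dose. Section 8.11 offers controls aged 30 and above two doses of ChAdOx1 nCoV-19, which includes controls in groups 9 and 10, but does not say whether the paracetamol advice applies. Table 14, which lists the procedures for those control doses, has no paracetamol step.

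**The case against.** The best reply is that this is an omission and not a clash. Section 8.10 does not exempt groups 9 and 10 from the limit, and Section 5 sets no different one. Section 5 leaves out the maximum for groups 4 and 6 too, so it can be read as a summary with the detail left to Section 8.10. Since the regimen is the same, a careful reader would probably carry the limit across. In addition, 6 g needs strict 4-hourly dosing through the night, paracetamol is only advised, the participant information and site instructions may state the limit, and few doses may remain to be given.

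Much of this stands. Silence is not an express permission to exceed 4 g, the 6 g figure is a worst case, and actual excess dosing is unknown. The control doses under Section 8.11 are weak evidence of continuing exposure, because the text does not link them to the advice.

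Two things remain. A daily maximum should not have to be inferred from a sentence that names other groups. And 6 g is not needed to pass the limit: one fifth dose does it, due at hour 16 or hour 20 under 4- or 5-hourly dosing. These replies limit the weight of the point but do not remove it.

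**Conclusion.** The concern holds as a minor point, worth correcting at the next opportunity. In the current text the only paracetamol maximum is written for groups 4 and 6, while groups 9 and 10 receive the same advice with none. Followed literally and at regular intervals, the instruction for participants aged 56 and over leads to 4 to 6 g in 24 hours, at worst 50% above the limit the protocol sets for the identical regimen.

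The totals assume fixed intervals starting at vaccination, with a dose falling exactly at hour 24 not counted. That Section 8.10 was overlooked when the older groups were added is inferred from the other three sections; it is not a stated decision. The mismatch in the text is certain. Any consequence for participants is not, because it depends on documents that are not available here.

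**What to change.** - In Section 8.10, change the group list to 4, 6, 9 and 10.
- In Section 5, add the 4 g in 24 hours maximum or a cross-reference to Section 8.10. A cross-reference in Section 7.3.2.1 would complete the set.
- Check that the site instructions and participant information for groups 9 and 10 carry the same limit.

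The cost is two group numbers and a phrase or two in the next amendment, plus a short consistency check of the supporting documents. Nothing in the design or analysis changes.
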